## Populations for Analyses

The following study populations are defined and will be analyzed as specified below.

Intention to treat population: We will complete an intent to treat analysis by which all participants who received at least one dose of the lowest dose of investigational product, whose dosing went off the track, lost to follow up, non-compliance, protocol deviation, and withdrawal.

Any study participant on this trial (registered) but never got study treatment will be mentioned, including the reason(s) of their exclusion from the trial.

### Safety Analyses

System Organ Class (SOC) will present the severity, frequency, and relationship of AEs to study intervention will be presented by System Organ Class (SOC). The start date, stop date, severity, relationship, expectedness, outcome, and duration of each AE will be reported. Serious treatment-emergent AEs will be presented with descriptions of causality and management.

### Baseline Descriptive Statistics

The primary statistical analysis will be a descriptive summary of the pattern of incidence and severity of adverse events across dosage levels. Conventional summary statistics will describe baseline characteristics and other outcomes (means, standard deviations, and medians, range and interquartile range (IQR) for numerical variables; counts and percentages for categorical variables). Summaries will be provided both overall and by dosage level. Medians, ranges and IQR, will be provided for the concentrations of CBD, THC and the primary metabolites at each sampling point. The ratio of parent compound concentration to metabolites will also be summarized to explore variability in cannabinoid metabolism. System organ class will present the severity, frequency, and relationship of treatment-emergent AEs to study intervention. The start date, stop date, severity, relationship, expectedness, outcome, and duration of each AE will be reported. Serious treatment-emergent AEs will be presented either in a table or a listing. The secondary outcomes, including pain, sleep impairment, depression, positive affect, anxiety and goal attainment scores, will be summarized at each timepoint; change from baseline will also be reported (both absolute and percentage change).

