| Statistical Methodology | *Sample Size determination:*  Precedent suggests that a power calculation is not appropriate for a dose-finding study. The study site and the number of planned dose escalations are standard for clinical trials.  *Populations for Analyses:*  We will complete an intent to treat analysis. All participants who received the investigational product for at least one month will be included in the analysis to ensure that these data would be likely to represent the effects of the study intervention.  *Safety Analyses:*  The severity, frequency, and relationship of AEs to study intervention will be presented by System Organ Class (SOC). The start date, stop date, severity, relationship, expectedness, outcome, and duration of each AE will be reported. Serious treatment-emergent AEs will be presented either in a table or a listing.  *Baseline and Descriptive Statistics:*  We will perform the descriptive statistics to describe baseline characteristics and other outcomes. The proportions and frequencies will be used to categories the categorical variable. The mean, median, range or standard deviations will be used to categories the continuous endpoints. Subgroup summarization based on dose level or other criteria may also be conducted. Median concentrations of CBD, THC and the major metabolites will be reported with ranges for each sampling time point. The ratio of parent to metabolites will be reported to provide estimates of the variability in cannabinoid metabolism.  *Sub-Group Analyses:*  We will perform prespecified subgroup analysis of primary and secondary outcomes-based sex and dose. |

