# STUDY INTERVENTION DISCONTINUATION AND PARTICIPANT DISCONTINUATION/WITHDRAWAL

## Dose limiting toxicity and Discontinuation of Study Intervention

Adverse events are categorized using the Common Terminology Criteria for Adverse Events (CTCAE version 5.0 dated 27 Nov 2017). If any of the following occur the participant will not move up to the next dose level (dose limiting toxicities):

1. Parental/youth report complaints of moderate mood elevation defined as exaggerated feelings of well-being which is disproportionate to the events and stimuli (Euphoria Grade 2)
2. Somnolence Grade 2 which includes moderate sedation (sleepiness and drowsiness) that limits instrumental activities of daily living
3. Cannabis-attributed diarrhea, Grade 2 or more defined as an increase of 4 - 6 stools per day over baseline; moderate increase in ostomy output compared to baseline; limiting instrumental activities of daily living
4. Unexplained tachycardia (w/out pain, fever, anemia etc.) requiring medical intervention
5. Unexplained hypotension requiring medical intervention
6. Non-infectious conjunctivitis Grade 2 defined as moderate decrease in visual acuity (best corrected visual acuity 20/40 and better or 3 lines or less decreased vision from known baseline) characterized by inflammation, swelling and redness to the conjunctiva of the eye.
7. Serious adverse events requiring hospitalization
8. Discretion of the participant, physician, or parents

Discontinuation from the study intervention does not mean interruption from the study, and remaining study procedures should be completed as indicated by the study protocol.

There will be no replacement of the study participants who were administered the investigational product, withdraw from the study, and lose follow-up (after signing an informed consent form). The main reason for the withdrawal of participants from the study will be noted in the participant's Case Record Form (CRF). The site investigator should contact the participants who fail to report during the follow-up visits which will be documented in the CRF.

Adverse events (AEs) and SAEs (Serious Adverse Events) will be reported according to Health Canada and Institutional regulations and reviewed by the data safety monitoring board (DSMB). The DSMB will hasten safety review if death is deemed related or potentially relevant to CBD-enriched CHE used in the study as the investigational product.

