### Time Period and Frequency for Event Assessment and Follow-Up

The occurrence of an adverse event AE or SAE may come to the attention of study personnel during study visits and interviews of a study participant presenting for medical care or upon review by a study monitor.

All AEs, including local and systemic reactions not meeting SAEs' criteria, will be captured on the appropriate case report form (CRF) of REDCap. Information to be collected includes event description, time of onset, clinician's assessment of severity, relationship to study product (assessed only by those with the training and authority to make a diagnosis), and time of resolution/stabilization of the event. All AEs occurring while on the study must be documented appropriately regardless of relationship. All AEs will be followed to an adequate resolution.

Any medical condition present at the time that the participant is screened will be considered a baseline and not reported as an AE. However, if the study participant's condition deteriorates during the study, it will be recorded as an AE. Changes in the severity of an AE will be documented to allow an assessment of the duration of event at each level of severity to be performed. AEs characterized as intermittent require documentation of onset and duration of each episode.

The study team will record all reportable events with start dates occurring any time after informed consent is obtained and for the duration of study participation. At each study visit, the investigator will inquire about the occurrence of AE/SAEs since the last visit. Events will be followed for outcome information until resolution or stabilization.

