# STATISTICAL CONSIDERATIONS

## Statistical Hypotheses

The primary endpoint (adverse events) will be analysed and presented descriptively with frequency counts and severity criteria. There are no pre specified statistical hypothesis.

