## Sample Size Determination

The CAN-CHA trial is a tolerability study designed to identify a safe dose of a cannabis product in adolescents with chronic headache. Because of the within-participant study design, a sample size of 20 study participants should provide a reasonable characterization of the pattern of adverse event frequency and severity as dosage increases. To provide more generalizable data, we will recruit these 20 study participants across three chronic pain programs in Halifax, Vancouver, and Toronto.

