### Sub-Group Analyses

We will perform subgroup analysis of primary and secondary endpoints based on sex and dose levels.

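### The primary by-dose adverse event summary covers, at levels 2 to 4, only participants who passed the level below, and it leaves the drug-free month unused as a reference, so it can understate how risk rises with dose

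*Protocol*

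**What the plan says.** The primary analysis is set in section 10.3.2, Baseline Descriptive Statistics: "The primary statistical analysis will be a descriptive summary of the pattern of incidence and severity of adverse events across dosage levels". That section also promises overall summaries. The endpoint in the synopsis is treatment-emergent adverse events.

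Each participant is due to pass through four monthly dose levels. The section on dose-limiting toxicity says: "If any of the following occur the participant will not move up to the next dose level (dose limiting toxicities". The same section and the one on withdrawal state that dosed participants who leave are not replaced.

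The purpose is given under Sample Size Determination: "The CAN-CHA trial is a tolerability study designed to identify a safe dose of a cannabis product". The same section says that "a sample size of 20 study participants should provide a reasonable characterization of the pattern of adverse event frequency and severity as dosage increases". The Study Rationale adds that the ideal tolerated dose will be carried into a later randomised trial. Neither place gives a numerical criterion for a safe or tolerated dose.

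Month 1 is drug-free, and dosing begins the day after visit 2. Adverse events are nevertheless captured from the start: "The study team will record all reportable events with start dates occurring any time after informed consent is obtained". The Schedule of Activities has them reviewed at visit 2. No section makes this month a comparator for the adverse event summary.

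**The concern.** The escalation rule removes from each higher level the participants who did badly at the one before. A by-level table then sets all dosed participants at level 1 beside a shrinking and selected group at level 4. If participants differ in susceptibility, those remaining are the more tolerant ones, and the displayed risk rises less steeply than it would if all had been exposed.

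Even without that distortion, a constant rate per level can hide substantial cumulative failure. A dose might be called tolerated on a low rate among the few who reached it.

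A second gap is background. Drowsiness, fatigue and insomnia are listed product risks, and the Background describes fatigue, sleep disruption and daytime sleepiness as common in this population. Without a zero-dose column, the table cannot show how much of the reported frequency would have arisen anyway.

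At stake is the dose taken forward to the later trial.

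**Working it through.** **The plan's own figure.** There is nothing to reproduce. N = 20 comes with no rate, precision target or power; the protocol states "There are no pre specified statistical hypothesis" and "Precedent suggests that a power calculation is not appropriate for a dose-finding study". The toxicity rates below are assumptions.

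**Step 1: attrition.** Let h be the chance of a dose-limiting toxicity at each level, the same at all four.
- Expected number starting level 4 = 20(1 − h)³.
- Share never reaching level 4 = 1 − (1 − h)³.
- Share failed by the end of level 4 = 1 − (1 − h)⁴.

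| h per level (assumed) | Start level 4 | Never reach level 4 | Failed by end of level 4 |
|---|---|---|---|
| 5% | 17.1 | 14% | 19% |
| 10% | 14.6 | 27% | 34% |
| 15% | 12.3 | 39% | 48% |
| 20% | 10.2 | 49% | 59% |

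In every row the rate among those at the level is flat by construction. Adding an assumed 5% monthly dropout reduces those starting level 4 to 12.5, 10.5 and 8.8 for h = 10%, 15% and 20%.

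**Step 2: the choice of denominator does not cure this.** At h = 10%, dividing by those at the level shows 10% throughout. Dividing plain event counts by all 20 gives 14.6 × 0.10 / 20 = 7.3% at level 4, an apparent fall.

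**Step 3: precision at the top.** With zero events in n, the exact 95% upper limit is 1 − 0.025^(1/n): 17% for n = 20, 22% for n = 15, 26% for n = 12 and 31% for n = 10.

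**Step 4: distortion of the dose pattern.** Assume logit(risk) = −3.3 + 2.0 × dose + a participant effect with SD 2, at the mid-doses 0.3, 0.5, 0.7 and 0.9 mg/kg/day. Risk if all were exposed rises 15%, 19%, 24%, 28%. What the table shows depends on the share of events that stop escalation:

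| Events stopping escalation | Displayed at levels 1 to 4 |
|---|---|
| All | 15%, 14%, 14%, 14% (12.6 of 20 enter level 4) |
| 25% | 15%, 18%, 21%, 24% (17.4 enter level 4) |
| 10% | 15%, 19%, 23%, 27% |

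Now keep every event as a stopper but change the SD, resetting the intercept so that level 1 is about 15%. With SD 1 the display rises from 15% to 25%. With SD 0 it rises from 15% to 37%, with no bias.

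A different model gives the same direction. Take 30% sensitive participants (event risk 30%, 50%, 65%, 75% by level) and 70% robust (5%, 7%, 9%, 11%), every event stopping escalation. The full-exposure risk is 12.5%, 19.9%, 25.8%, 30.2%; the displayed risk is 12.5%, 17.3%, 17.2%, 14.9%.

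**Step 5: background.** If an untreated symptom has monthly risk b, the share with it at least once in four months is 1 − (1 − b)⁴: 34% at b = 10% and 76% at b = 30%, with no drug effect. For one month at b = 30%, an added drug risk a of 0, 10% or 20% gives 1 − (1 − b)(1 − a) = 30%, 37% or 44%. These figures make no allowance for the rule that baseline conditions count only if they worsen.

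**The case against.** The strongest reply is that the effect may be small. The endpoint covers all treatment-emergent events, whereas escalation stops only for a short list: certain Grade 2 events, tachycardia or hypotension needing intervention, hospitalisation, or discretion. Step 4 bears this out: if a quarter of events or fewer stop escalation, most of the rise remains visible. The maximum CBD dose is also described as under a tenth of that in earlier paediatric studies. This stands, and it limits the size claimed. It does not remove the selection.

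Per-level denominators may be set in an SAP not shown, and attrition could be rebuilt from the overall summaries, event dates and individual listings. That is also true. But the protocol itself names the primary analysis, and Step 2 shows that neither obvious denominator repairs it.

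Background is partly handled: history is CTCAE-graded at visit 1, pre-existing conditions count only if they worsen, and causality is assessed. These rules do not estimate how often untreated symptoms arise or worsen.

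Some stronger readings are not supported:
- A reader might infer that a flat safety profile is to be expected. It appears only under particular assumptions.
- A reader might take cumulative failure as the share never reaching the top level. In the first row of Step 4, 46% fail by the end but 37% never reach level 4 (1 − 12.6/20); at a constant 10% the figures are 34% and 27%.
- A reader might infer that held participants accumulate extra low-dose exposure, or that weaning weeks are pooled with treatment months. The protocol states neither.
- The plan says "We will perform subgroup analysis of primary and secondary endpoints based on sex and dose levels". A reader might want dose removed from that list, but this is a matter of labelling and correcting the primary summary does not require it.

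**Conclusion.** The point holds in a bounded form. By the protocol's own escalation and no-replacement rules, the primary summary at levels 2 to 4 is conditional on having passed the level below. Level 1 is unselected if the at-least-one-dose population of section 10.3 applies. The synopsis instead requires at least one month of product, which would drop early stoppers; the two must be reconciled.

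Where susceptibility varies between participants, the bias runs towards safety. Its size rests on rates the protocol does not give: at 5% toxicity per level about one in seven never reach level 4, and at 10% or more it is over a quarter. Distortion of the all-event pattern ranges from none to nearly complete flattening across the settings tried.

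The absence of an untreated reference is a gap in the planned summary and not in the data. This should be corrected, because the tolerated-dose conclusion depends on the summary.

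**What to change.** Amend section 10.3.2 (analysis only):

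1. Beside the by-dose adverse event table, report for each level the number entering it. Add the cumulative proportion of all dosed participants with a dose-limiting toxicity or adverse-event discontinuation by that level, with exact 95% intervals. Show discretionary non-escalation and other withdrawals separately, since discretion is one of the listed reasons for not escalating and need not reflect intolerance. State that the tolerated-dose conclusion rests on this cumulative figure.
2. Add the run-in month (visit 1 to visit 2) as a descriptive zero-dose column, noting that dose order is confounded with time, so the column gives context and not a clean drug effect.
3. Tabulate weaning-period events separately from the escalation months, because Table 5 revisits three of the dose ranges for one week each.

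The cost is protocol and SAP wording and one extra table. No new data are needed. The tolerability figure may turn out less favourable.

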### Sub-Group Analyses

We will perform subgroup analysis of primary and secondary endpoints based on sex and dose levels.

### Tabulation of Individual participant Data

Individual participant data will be listed by measure and time point.

# SUPPORTING DOCUMENTATION AND OPERATIONAL CONSIDERATIONS

## Regulatory, Ethical, and Study Oversight Considerations

### Informed Consent Process

#### Consent/assent and Other Informational Documents Provided to participants

Consent forms describing the study intervention, study procedures, and risks are given to the participant, and written documentation of informed consent is required before starting intervention/administering study intervention.

#### Consent and Assent Procedures and Documentation

Informed consent/assent is a process that is initiated before the individual agrees to participate in the study and continues throughout the individual’s study participation. Consent and assent forms will be Research Ethics Board (REB)-approved, and the participant will be asked to read and review the document. The site investigator will explain the medical part of the research study to the participant and answer any questions that may arise. A verbal explanation will be provided in terms of the participant’s comprehension of the purposes, procedures, and potential risks of the study and their rights as research participants. Caregivers (if applicable) and/or participants will have the opportunity to carefully review the written consent and/or assent form(s) and ask questions before signing. The participants should have a chance to discuss the study with their family or surrogates or think about it before agreeing to participate. The caregiver and/or participant will sign the informed consent and/or assent document(s) before any procedures being done specifically for the study. Caregivers and/or participants must be informed that participation is voluntary and that they may withdraw from the study at any time without prejudice. A copy of the informed consent/assent document(s) will be given to the participants for their records. The informed consent/assent process will be conducted and documented in the source document (including the date). The rights and welfare of the participants will be protected by emphasizing to them that the quality of their medical care will not be adversely affected if they decline to participate in this study.

#### Study Discontinuation and Closure

This study may be temporarily suspended or prematurely terminated if there is sufficient reasonable cause. Written notification, documenting the reason for study suspension or termination, will be provided by the suspending or terminating party to study participants, investigator, funding agency, and regulatory authorities. Suppose the study is prematurely terminated or suspended. In that case, the site Qualified investigator (QI) will promptly inform study participants, the REB, and the sponsor and will provide the reason(s) for the termination or suspension. Study participants will be contacted, as applicable, and be informed of changes to the study visit schedule.

Circumstances that may warrant termination or suspension include, but are not limited to:

- Determination of unexpected, significant, or unacceptable risk to participants
- Demonstration of efficacy that would warrant stopping
- Insufficient compliance to protocol requirements
- Data that are not sufficiently complete and/or evaluable
- Determination that the primary endpoint has been met
- Determination of futility

The study may resume once concerns about safety, protocol compliance, and data quality are addressed and satisfy the sponsor and/or REB.

### Confidentiality and Privacy

Participant confidentiality and privacy is strictly held in trust by the participating investigators, their staff, and the sponsor(s) and their interventions. This confidentiality is extended to cover the testing of biological samples in addition to the clinical and genetic information relating to participants. Therefore, the study protocol, documentation, data, and all other information generated will be held in strict confidence. Furthermore, no information concerning the study of the data will be released to any unauthorized third party without the prior written approval of the sponsor.

All research activities will be conducted in as private a setting as possible.

The study monitor, other authorized representatives of the sponsor, representatives of the Research Ethics Board (REB), regulatory agencies may inspect all documents and records required to be maintained by the qualified investigators, including but not limited to medical records (office, clinic, or hospital) and pharmacy records for the participants in this study.

The study participant’s contact information will be securely stored at each clinical site for internal use during the study. At the end of the study, all records will continue to be kept in a secure location for at least 15 years after study completion per Health Canada requirement, and as long as dictated by the reviewing REB, Institutional policies, or sponsor requirements.

Study participant research data, which is for statistical analysis and scientific reporting, will be transmitted to and stored at the Women and Children’s Health Research Institute, University of Alberta. Edmonton. This will not include the participant’s identifying information. Rather, individual participants and their research data will be determined by a unique study identification number. The study data entry and study management systems used by clinical sites will be secured and password protected. At the end of the study, all study data will be archived at University of Manitoba.

